**Figure 1. F1:**
[figure not shown]
The data collection workflow. ^a^Data to establish the gold standard. AI: artificial intelligence; AVIRI: AI for disease-related visual impairment screening using retinal imaging; IOP: intraocular pressure; VA: visual acuity.

##### Intervention Arm

Patients randomized to the AI-assisted arm will undergo retinal photography, with their images analyzed on-site by AVIRI. Fundus images will be checked by onsite optometrists, with poor-quality photographs retaken on the spot. If adequate quality still cannot be obtained, the participant’s ID will be recorded in the study log. The AVIRI report will also include a quality-check notification indicating when an image does not pass its internal quality assessment, alerting the clinical optometrists that the AI-generated results may be affected. If a case is detected by AVIRI as having disease-related VI, the retinal images and AVIRI report will be sent to an assigned clinical optometrist via the institution’s secured Microsoft Teams for further evaluation (Microsoft Corp). Clinical optometrists, who are independent from the onsite screening team, will examine the AI-generated results and make the final referral decision. Only cases identified as positive by the AVIRI model are reviewed by the clinical optometrists, and the referral process follows the same standardized procedure applied across both study arms. Similarly, after the referral decision, participants will complete a patient-acceptance questionnaire to assess their perceptions and satisfaction with the AI-assisted model. Finally, anterior eye photography and subjective refraction will be performed to establish the ground truth status (Figure 1).

### Data Quality Assurance

A senior data coordinator will oversee all data entry procedures to ensure consistency and accuracy throughout the process. Each data entry will be independently verified by a separate data entry personnel to minimize errors and discrepancies. Regular checks will be conducted to ensure that all consented, eligible participants’ data have been properly entered into the system. Additionally, basic tabulation will be performed against the study screening log, and any inconsistencies will be promptly addressed to maintain the integrity of the data. To ensure consistent image quality, all imaging personnel will undergo standardized training and certification in retinal photography. Fundus cameras will be calibrated according to manufacturer guidelines. Images will be captured following a standardized protocol for field of view, focus, and illumination and reviewed in real time. Ungradable images will be repeated onsite and flagged in the data log. Image quality will be graded as good, borderline, or poor. A detailed review process will be implemented to guarantee the accuracy and completeness of the dataset before analysis.

### Data Entry and Storage

Data will be recorded on paper forms and subsequently entered into a password-protected Excel spreadsheet stored on an encrypted storage drive. Slit lamp and retinal photographs will be deidentified and stored in digital format for grading purposes. A digital audio recorder will be used during the patient acceptance questionnaire to facilitate accurate documentation, analysis, and review of discussions. A distinct section in the consent form will be used to obtain participants’ permission for audio recording their responses. The recorded audio data will be transcribed and translated into English (if required) by study team members after the participant’s visit. The data entry process will be supervised by a data coordinator, and all entered data will be independently verified by another data entry personnel.

All data files will be encrypted to ensure data security. Access keys for encryption will be securely stored and made available only to study team members. Data access and key management will adhere to Singhealth’s data retention policy. Case files will be securely stored with restricted access, in accordance with the study delegation log.

Participants’ confidentiality and privacy will be upheld throughout the study, from the initial data collection phase until the secure destruction of personal and sensitive information. Only authorized research team members will have access to research data.

### Outcome Measures

#### Ground Truth Establishment

The ground truth diagnosis will be determined by a panel of 3 board-certified ophthalmologists, who will independently review presenting VA, best-corrected VA data, intraocular pressure measurements, medical history, and anterior and retinal photographs. The reference standard outcome (refer vs not refer) will be determined by majority agreement (2 out of 3 panel experts). Cases without a clear majority (eg, ungradable) will undergo consensus discussion among the experts, and if consensus cannot be reached, a senior ophthalmologist will adjudicate. The adjudicator will not be blinded by the clinical context as it is required to make a referral decision. To ensure the credibility of the pRCT results, the panel of three board-certified ophthalmologists will be blinded to the participants’ group assignments to minimize bias, and they will not participate in any study procedures that could compromise or reveal participants’ randomized group assignments.

#### Primary Outcomes

The primary outcome is the rate of correct referrals based on the reference standard. A correct referral was defined as a case in which the AI or optometrist’s referral decision (refer vs no refer) matched the ground truth outcome determined by the panel of three board-certified ophthalmologists. To evaluate whether the AI-assisted model offers improved referral accuracy compared to the traditional screening model, performance metrics such as accuracy, AUC, sensitivity, and specificity will be calculated and compared for both models. A calibration plot will be used to assess the agreement between the model’s predicted probability of VI and the actual VI outcomes. Performance metrics will also be stratified and analyzed according to the severity of VI. Moderate VI is defined as presenting VA between 6/12 and 6/48, while severe VI is defined as presenting VA of 6/60 or worse [12].

#### Secondary Outcomes

The secondary outcomes of this pRCT include operational efficiency, acceptability, perceived feasibility, and cost evaluation. These secondary outcomes are important for successful implementation and future scalability.

##### Operational Efficiency

This evaluation will assess the effectiveness of the screening workflow by measuring the average time required per patient to complete the entire screening process, providing insights into overall efficiency. The screening capacity will be evaluated by calculating the average number of patients screened per hour. In addition to the average number of patients screened per hour and average time per patient, we will break down the total screening time into specific workflow steps (eg, retinal photo taking, results analysis, review, and referral decision making) to allow a more detailed comparison of operational efficiency between the traditional and AI-assisted arms. These metrics will help determine whether the AI-assisted model improves workflow efficiency compared to the current screening approach.

##### Acceptability

In this study, acceptability is defined as patients’ perception of the AI-assisted screening model in terms of its usability, comfort, and overall satisfaction [13]. All participants randomized to either the AI-assisted or traditional screening arm will be invited to complete a structured questionnaire designed to assess their perception and satisfaction with the screening process. The questionnaire consists of 3 items rated on a 5-point Likert scale, evaluating the overall satisfaction with the screening process [14]. Five dichotomous questions are also included to evaluate factors such as awareness of AI and confidence in results. The questionnaire was developed following established psychometric principles to ensure validity and reliability in assessing patient perspectives [15].

To enhance the accuracy of data collection, trained research coordinators will administer the questionnaire with audio recording after obtaining patients’ consent. The responses will be transcribed verbatim. This approach ensures consistency in responses, minimizes misinterpretation of questions, and allows coordinators to clarify any concerns raised by participants. Missing questionnaire items will be reported as nonresponses. Given the short questionnaire and supervised administration, minimal missing data are expected. However, sensitivity analyses will be conducted if missingness exceeds 5%. Insights gained from this assessment will help refine the implementation of AI-assisted screening models and address potential barriers to patient acceptance.

##### Feasibility

Feasibility is defined as the degree to which the AI-assisted screening model can be effectively implemented within the intended setting [13]. Service providers’ perceptions of feasibility will be assessed through focus group discussions. The results from evaluations of operational efficiency and patient acceptability, as described earlier, will inform the development of discussion questions based on the constructs of the Consolidated Framework for Implementation Research (CFIR), a well-established framework for assessing the implementation of health care innovations. The CFIR provides a structured approach for understanding the factors that influence successful adoption and integration of new interventions within health care settings [16].

Focus group discussions will be conducted with optometrists, each lasting 60 to 90 minutes, with the objective of achieving both data saturation and meaning saturation [17]. All seven clinical optometrists who reviewed the AVIRI output will be invited to join the focus group discussions. The FGD will enable us to capture diverse perspectives and stakeholder experiences with the AI workflow. The focus group discussions will be audio-recorded, transcribed verbatim, and analyzed using framework analysis [18]. Two trained researchers will conduct both inductive and deductive coding, with a third researcher moderating if discrepancies arise after a consensus discussion. The analysis will be interpreted through the lens of the CFIR framework [16]. This in-depth approach will help identify barriers and enablers to the implementation of the AI-assisted screening model from the service providers’ perspectives, facilitate the development of meaningful adjustments to the model, and uncover potential strategies for improving future implementations.

##### Cost Evaluation

We will assess the incremental cost savings of implementing the AI-assisted screening model compared to the traditional screening model using an Activity-Based Costing (ABC) approach. The analysis will include all nonsunk costs incurred up to the referral decision. These costs include labor, materials, supplies, and amortized expenses for technology and space use. Costs will be grouped according to the key activities of each screening model, such as conducting the screening examinations, running the AVIRI algorithm, and generating on-site test results. Fixed costs will be amortized based on the expected useful life of the involved fixed assets. For clinical assessment costs, we will use nonsubsidized billing rates, as these are expected to closely reflect actual costs [19]. As the study involves only a one-time screening visit without longitudinal follow-up, all cost calculations will reflect a cross-sectional time frame, limited to the immediate costs incurred during the single-visit screening encounter.

### Data Analysis Plan

#### Model Performance

The AI model was based on the ViT-base backbone, which was initialized using pretrained weights obtained through supervised learning on the ImageNet-21k dataset [20]. Fine-tuning was carried out for 40 epochs to allow for sufficient learning while reducing the risk of overfitting. The process was performed using a batch size of 16, with a fixed learning rate of 1 × 10⁻⁵, weight decay set at 5 × 10⁻⁴, and the default drop path rate applied. To evaluate the effectiveness of the AI-assisted screening model compared to the traditional screening model in detecting VI, both models will be assessed against the ground truth. Overall accuracy, sensitivity, and specificity will be calculated and compared using *z* tests for 2 proportions. Additionally, AUC and the area under the precision-recall curve will be determined for each model. Differences in AUC and area under the precision-recall curve between the two models will be analyzed using bootstrap resampling. All quantitative analyses for model performance will be conducted using R, including diagnostic accuracy metrics and comparative statistical tests.

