### Hypothesis and Objectives

This study is designed as a hybrid type 1 effectiveness-implementation trial to evaluate and compare the performance, operational efficiency, acceptability, feasibility, and cost differences between the AI-assisted screening model and the traditional screening model in a community screening setting. A pragmatic randomized controlled trial (pRCT) design will be used to better represent the targeted real-world population. This study will focus on the following specific aims:

Aim 1: To evaluate and compare the referral accuracy between the AI-assisted screening model and traditional screening model for disease-related VI.

Hypothesis 1: The AI-assisted screening model will outperform the traditional screening model in detecting and referring VI cases.

Aim 2: To compare the operational efficiency and acceptability between the AI-assisted screening model and the traditional screening model, and to investigate the feasibility of the AI-assisted screening model.

Hypothesis 2: The AI-assisted screening model will demonstrate greater operational efficiency and acceptability compared to the traditional screening model and will be feasible for implementation in community-based settings.

Aim 3: To compare the overall costs of the AI-assisted screening model and the traditional screening model from a health system perspective.

Hypothesis 3: The AI-assisted screening model will be more cost-effective than the current traditional screening model from a health system perspective.

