### Sample Size Calculation

This study will recruit a total of 1000 participants aged 50 years and older using a 2-arm pRCT design with broad inclusion criteria based solely on age. Of these, 500 participants are targeted to have presenting VA better than 6/12 (L1), a number determined based on operational feasibility in community screenings.

Participants with presenting VA worse than 6/12 (L2) will be randomized to either the AI-assisted or traditional screening model. Sample size estimation for this randomized comparison was based on an assumed accuracy of 70% for the current traditional screening model and prevalence of 18% for any VI, 11% for disease-related VI, and 8% for refractive-error related VI (prevalence estimates were based on the SEED study) [2]. Detecting a clinically meaningful difference of 10% between the 2 screening models with 80% statistical power at a 5% 2-sided type I error requires 250 participants per arm. Therefore, a total of 500 randomized participants (L2) will be included in the primary analysis.

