### Randomization

VI is defined according to the United States VI definition as having a presenting VA worse than 20/40 (equivalent to 6/12) in the better-seeing eye [3]. Participants with presenting VA of 6/12 or better (L1) will not be randomized. These participants will receive a basic ocular assessment, including fundus photography and anterior eye imaging. The collected images will not be used in the comparative analysis between the AI-assisted and traditional screening arms.

Participants with presenting VA worse than 6/12 (L2) will be randomized into either the AI-assisted screening arm or the traditional screening arm using a 1:1 allocation ratio. Randomization will be conducted at the patient level, ensuring that both eyes of the same participant are assigned to the same study arm. The randomization sequence will be generated by an independent statistician using the “randomizeR” package in R statistical software. This approach ensures an unbiased allocation process while maintaining the integrity of the study design.

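### The primary accuracy comparison leaves presenting VA and age unused; prespecifying an adjusted risk difference would be a free, probably modest, gain in precision

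*Protocol article*

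**What the plan says.** - **Outcome.** Under Primary Outcomes: "The primary outcome is the rate of correct referrals based on the reference standard". A participant counts as correct when the refer/not-refer decision agrees with the ophthalmologist panel, so this rate is overall accuracy.
- **Test.** Under Model Performance: "Overall accuracy, sensitivity, and specificity will be calculated and compared using" z tests for two proportions. No covariate is named for this comparison.
- **What is known before allocation.** Under Randomization: "Participants with presenting VA worse than 6/12 (L2) will be randomized into either the AI-assisted screening arm or the traditional screening arm". Presenting VA therefore decides who is randomized. Age is the only inclusion criterion (Sample Size Calculation). Allocation is 1:1 by participant, and no stratification factor is described.
- **Severity.** Under Primary Outcomes: "Performance metrics will also be stratified and analyzed according to the severity of VI". The severity classes are defined by presenting VA. This is an additional breakdown and does not enter the main comparison.
- **Sample size basis.** "assumed accuracy of 70% for the current traditional screening model", then "Detecting a clinically meaningful difference of 10% between the 2 screening models" "with 80% statistical power at a 5% 2-sided type I error", giving 250 per arm.

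**The concern.** When baseline variables predict the outcome, a two-proportion test treats the variation they explain as noise. Adjusting for them gives a narrower interval for the same marginal difference and corrects for chance imbalance between arms. Both variables are complete here by design: a participant cannot be randomized without a presenting VA, or enter the study without a known age.

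Presenting VA could plausibly predict correctness. It is one of the items the panel reviews in setting the reference standard (Ground Truth Establishment), so it feeds one side of the match that defines the outcome. It still varies within the randomized group, from just worse than 6/12 to 6/60 or worse. The case for age is weaker: the Introduction attributes about half of VI to age-related disease, which bears on who needs referral but not directly on whether the decision is right.

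At stake is some width of the confidence interval and a few points of power. The validity of the result is not at stake.

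**Working it through.** **Inputs.** Control accuracy 0.70, absolute difference 0.10, two-sided 5%, 80% power and 250 per arm come from Sample Size Calculation. The direction (0.80 in the AI-assisted arm) comes from Hypothesis 1: "The AI-assisted screening model will outperform the traditional screening model in detecting and referring VI cases". R² is the share of variance in correctness explained by presenting VA and age. The documents do not give it, so it is an assumption shown as a range that starts at zero.

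**Step 1: the plan's own figure.** Pooled two-proportion formula with mean rate 0.75:

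n = [1.960·√(2·0.75·0.25) + 0.8416·√(0.21 + 0.16)]² / 0.10² = (1.2002 + 0.5119)² / 0.01 = 293.2, so 294 per arm.

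The stated 250 is not reproduced. The unpooled form gives 291 and the arcsine form 292.

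**Step 2: unadjusted power at 250 per arm.**

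Φ[(0.10·√250 − 1.2002) / 0.6083] = Φ(0.626) = 73.4%.

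The 95% CI half-width is 1.96·√((0.21 + 0.16)/250) = 7.5 points.

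**Step 3: power with adjustment.** Replace 250 by an effective n of 250/(1 − R²), and multiply the half-width by √(1 − R²).

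| Assumed R² | Effective n per arm | Power | Half-width (points) |
|---|---|---|---|
| 0% | 250.0 | 73.4% | 7.5 |
| 1% | 252.5 | 73.9% | 7.5 |
| 2% | 255.1 | 74.3% | 7.5 |
| 5% | 263.2 | 75.6% | 7.3 |
| 10% | 277.8 | 77.8% | 7.2 |
| 15% | 294.1 | 80.1% | 7.0 |

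**Step 4: R² needed to reach 80% by adjustment alone.** 1 − 250/294 = 15.0%.

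**Step 5: check by simulation.** 20,000 trials per scenario, one normally distributed covariate, and an adjusted risk difference from a linear model with robust standard error. This is a stand-in for the standardized logistic estimate, not that estimator itself.

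| R² | Unadjusted power | Adjusted power |
|---|---|---|
| 0% | 73.5% | 73.8% |
| 1.6% | 73.9% | 74.5% |
| 4.3% | 74.3% | 76.1% |
| 10.1% | 73.6% | 77.9% |
| 14.6% | 73.5% | 79.7% |

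Monte Carlo error is about √(0.735·0.265/20,000) = 0.3 points, so the simulation agrees with the approximation in Step 3.

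**The case against.** The strongest reply is that nothing here is an error. With 1:1 allocation by participant and no stratification factor described, the two-proportion z test is valid and matches the basis of the sample size. That stands. A reader might infer from this point that the planned test is biased or wrong, and the documents do not support that.

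A second reply is that the loss of precision is assumed. That also stands. The outcome is whether the decision was correct, not whether referral was needed. Worse VA may predict the need for referral and yet say little about correctness, since errors run both ways. VA is also restricted to worse than 6/12 among those randomized, and nothing in the article links age to referral accuracy. A reader might take the planned breakdown by severity as the plan's own statement that accuracy varies with VA. It says only that the metrics will be broken down, and gives no size for any variation.

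A third reply is that covariate adjustment is often left to an analysis plan, and none is shown. This carries less weight. The article names the test for the primary comparison, so the suggestion is to replace a stated method. It does not complain of missing detail.

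**Conclusion.** A free improvement, not a defect. The planned primary analysis is valid but leaves aside two baseline variables that every randomized participant has. If R² lies between 1% and 5%, adjustment adds roughly 0.5 to 2 points of power, and the half-width narrows by about 0.2 points at most. At 10% the gain is about 4 points of power. These figures rest on 70% vs 80%, 250 analysed per arm and the effective-n approximation. No R² in the range is supported by the documents, and values near zero are possible.

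It is tempting to present adjustment as the remedy for the power shortfall. The documents do not support that. The shortfall (73.4% against the stated 80%; 294 per arm needed against 250) arises in Sample Size Calculation, not from the choice of test. Adjustment alone would close it only if R² reached about 15%. It should be dealt with as a separate matter.

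**What to change.** Before analysis starts (the article expects April 2026), prespecify as the primary estimate the standardized (marginal) difference in correct-referral rate, with a 95% CI, from a logistic model with arm, presenting VA (logMAR, continuous, better-seeing eye) and age. Averaging the model's predictions over all randomized participants keeps the quantity a difference in proportions, so the 10-point target still applies. Keep the two-proportion z test as a sensitivity analysis.

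Apply the same model to sensitivity and specificity only where the reference-positive and reference-negative subsets are large enough to support it; otherwise leave those comparisons unadjusted.

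The cost is a sentence in the analysis plan and a few lines of R, with no new data and no extra participants. The covariates and their form must be fixed before outcome data are seen by arm, because an adjustment chosen afterwards loses its credibility.

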## Methods

### AI Model Development and Validation

In a proof-of-concept study, AVIRI demonstrated high diagnostic performance, achieving an area under the receiver operating characteristic curve (AUC) of 0.942 (95% CI 0.922‐0.956), with an accuracy of 87.7%, sensitivity of 94.6%, and specificity of 81.3%, compared with the ground truth of ophthalmologists’ clinical diagnoses. External validation using population-based datasets from China, India, and Australia yielded AUCs ranging from 0.859 to 0.935, further supporting AVIRI’s robustness across different populations [8]. While these findings highlight the model’s ability to detect disease-related VI, its real-world performance in community-based settings with undilated eye examinations has not yet been explored.

To address this gap, a previous retrospective evaluation was conducted using 421 retinal images collected in a community setting with the Crystalvue retinal camera (Crystalvue NFC-700; Crystalvue Medical Corporation). This evaluation was part of pilot testing and was not previously published. Multiple domain adaptation strategies were applied to enhance model generalizability, and a ViT-Base architecture, trained on the SEED dataset, was selected as the optimal backbone. This adaptation achieved an AUC of 0.853, specificity of 0.688 (when sensitivity fixed at 80%), and *F*_1_ score of 0.347. Additionally, a user interface was developed to facilitate clinical integration, allowing researchers to input clinical data and generate automated diagnostic reports using AVIRI. These findings provide the foundation for further prospective validation, evaluating AVIRI’s real-world performance in an AI-assisted vision screening model.

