##### Control Arm

Participants will first sign informed consent before proceeding with any assessment. After being randomized into the traditional model arm, the screening will follow the standard examination workflow used in the traditional screening model, which consists of pinhole VA, intraocular pressure, auto refraction, slit lamp examination, and retinal photography. The fundus photographs will be reviewed by the onsite optometrists, and any images of insufficient quality will be retaken immediately to improve clarity. If image quality remains inadequate, the participant’s ID will be flagged in the study log. Referral decisions will be made by the onsite optometrists, incorporating the findings from all other screening tests. After receiving the referral outcome, participants will be invited to complete a patient-acceptance questionnaire to assess their perceptions and satisfaction with the traditional screening model (Multimedia Appendix 1). Finally, anterior eye photography and subjective refraction will be performed to establish the ground truth status for the referral decision (Figure 1).

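### The between-arm AUC and AUPRC tests do not say which output is ranked; using AVIRI's score would bias AUC towards AI, and using the final decision would only repeat sensitivity and specificity

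*Protocol article*

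**What the plan says.** The Model Performance section first compares accuracy, sensitivity and specificity between the arms with two-proportion z tests. It then adds: "Additionally, AUC and the area under the precision-recall curve will be determined for each model", and next: "Differences in AUC and area under the precision-recall curve between the two models will be analyzed using bootstrap resampling". Primary Outcomes also lists AUC among the measures for judging whether the AI-assisted model refers more accurately.

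The outputs available in each arm are as follows.

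- **Traditional arm** (Control Arm section): "Referral decisions will be made by the onsite optometrists, incorporating the findings from all other screening tests". No score or rating scale is described.
- **AI-assisted arm** (Intervention Arm section): AVIRI-positive cases go to clinical optometrists, who "will examine the AI-generated results and make the final referral decision". AVIRI-negative cases are not reviewed.
- **Outcome scale** (Primary Outcomes): a referral is correct when "the AI or optometrist’s referral decision (refer vs no refer) matched the ground truth outcome".
- **Calibration** (Primary Outcomes): a plot is planned of the model's "predicted probability of VI and the actual VI outcomes". This is the only planned analysis that expressly uses a probability from AVIRI.

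**The concern.** A ROC or precision-recall curve needs a graded output. The traditional arm has none, so its curve consists of one operating point joined to the corners. In the AI-assisted arm two outputs could be ranked, and the protocol names neither.

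- **AVIRI's probability.** The test then compares a full curve with a single point. A concave ROC curve always encloses more area than any one of its points joined to the corners, so the AI arm gains AUC even when underlying discrimination is equal. The quantity tested is also a component and not the randomised pathway, because an optometrist can overrule an AVIRI positive.
- **The final decision.** AUC is then the mean of sensitivity and specificity, both already tested.

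At stake is a supporting claim for Hypothesis 1, that the AI-assisted model outperforms the traditional one. On the first reading, a significant AUC difference could arise from the mismatch of scales alone.

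The calibration plan has a related wording fault. The Randomization section defines VI as presenting acuity worse than 6/12, and only participants below that same cut-off are randomised. Taken literally, calibration against VI has no non-events among randomised participants.

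**Working it through.** **Inputs.** From AI Model Development and Validation: community-image AUC 0.853, with specificity 0.688 at sensitivity 0.80; proof-of-concept AUC 0.942, with sensitivity 0.946 and specificity 0.813. From Sample Size Calculation: 250 per arm, and prevalences of 18% (any VI) and 11% (disease-related VI). The protocol gives no referable share for randomised participants. Assumed values are 0.30 and 11/18 = 0.61, with 0.10 added for one AUPRC check. The protocol states no power or error figure for the AUC test, so there is none to reproduce.

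**Step 1. AUC of a yes/no output.** Counting ties as one half:

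AUC = se·sp + ½[se(1 − sp) + (1 − se)sp] = (se + sp)/2.

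**Step 2. The same model on two scales.**

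| Model | As a score | As a decision | Gap |
|---|---|---|---|
| Community images | 0.853 | (0.80 + 0.688)/2 = 0.744 | 0.109 |
| Proof of concept | 0.942 | (0.946 + 0.813)/2 = 0.8795 | 0.0625 |

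**Step 3. Identical discrimination in both arms.** With equal-variance binormal scores, d′ = √2·z(0.853) = 1.484.

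- Best single cut: Φ(1.484/2) = 0.771.
- Cut at sensitivity 0.80: specificity Φ(1.484 − 0.842) = 0.740, so AUC (0.80 + 0.740)/2 = 0.770.

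The expected gap is therefore 0.082 to 0.083 with no true difference.

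**Step 4. Simulated test.** 250 per arm, unpaired percentile bootstrap with 200 resamples, 300 trials per scenario (Monte Carlo error about 3 points). The traditional arm is dichotomised. The AI arm is either left continuous or cut at the same point.

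| Referable share | Cut | AI continuous: mean AUC difference | AI continuous: AI declared better | Both binary: any rejection |
|---|---|---|---|---|
| 0.61 | se 0.80 | 0.085 | 65% | 4% |
| 0.61 | best | 0.083 | 64% | 5% |
| 0.30 | se 0.80 | 0.086 | 61% | 4% |
| 0.30 | best | 0.083 | 59% | 5% |

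A binormal curve fitted through the proof-of-concept AUC and operating point (share 0.61, 250 trials) gives 69%. With both arms binary, AI is declared better in only 2–3% of trials, which is the nominal rate for one tail.

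**Step 5. AUPRC.** With the score of Step 3 and the binary arm cut at sensitivity 0.80:

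| Referable share | Continuous | Binary, step-wise | Binary, trapezoid from (recall 0, precision 1) |
|---|---|---|---|
| 0.61 | 0.896 | 0.785 | 0.875 |
| 0.30 | 0.731 | 0.515 | 0.714 |
| 0.10 | 0.472 | 0.224 | 0.537 |

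Step-wise, the simulated test declares AI better in 79–87% of trials at shares 0.30 and 0.61. Under the trapezoid rule the gap nearly closes, and at a share of 0.10 it reverses.

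**The case against.** The strongest reply is that the biased comparison is not written in the protocol. The two models in the Model Performance section are the two screening pathways, and both end in a binary decision. On that reading the test holds its nominal error rate. Which output feeds each curve could also be left to an analysis plan that is not shown, and the primary analysis is the z test on correct referrals.

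Much of this stands. The continuous-score reading is an inference. It is plausible because a precision-recall curve has little purpose for a yes/no output, and because the protocol plans calibration of AVIRI's probability and reports its AUC beside a separate operating point. But the between-arm test itself is stated, not left open, and neither reading makes it useful.

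A reader might infer three stronger conclusions that the protocol does not support.

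- **That the plan favours AI by construction.** This holds for AUC only if the probability is ranked and the ROC curve is concave. It does not hold generally for AUPRC (Step 5). Randomisation also makes the referable shares equal in expectation, so differing prevalence between arms is not a systematic fault.
- **That the false-superiority rate is about 80%.** Setting the reported point (0.80, 0.688) against the equal-variance curve gives 79–81%. That curve has specificity 0.740 at sensitivity 0.80, so the point lies below it, and part of the gap is worse performance.
- **That the primary result is compromised.** It is not, because it uses the binary decision in both arms.

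**Conclusion.** The concern holds in conditional form. The planned between-arm AUC and AUPRC tests are either misleading or redundant, depending on an output that the protocol does not name.

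If AVIRI's probability is ranked, AI would be declared better on AUC in about 60–65% of trials with no difference in discrimination. This assumes equal-variance binormal scores with AUC 0.853 in both arms, a referable share of 0.30 to 0.61 and 250 per arm. It also credits the traditional arm with a latent score that is only hypothetical. The pilot gap of 0.109 needs none of these assumptions, but it describes AVIRI against itself and not against optometrists. No single size or direction can be given for AUPRC.

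This should be fixed because it could produce a false supporting claim. It does not threaten the primary comparison. The calibration outcome may be shorthand for disease-related VI, which is what AVIRI is said to detect, and needs only correct naming.

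**What to change.** 1. Delete the bootstrap tests of AUC and AUPRC between the arms.
2. Compare the arms only on the final referral decision: accuracy, sensitivity and specificity, each difference with a confidence interval.
3. Report AUC, AUPRC and calibration for AVIRI alone and label them descriptive. Name the ranked output (AVIRI's probability) and the AUPRC interpolation rule. Use the panel's reference outcome or disease-related VI as the target, not VI.

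This is a change of wording that can be made before analysis begins, which the Results section expects in April 2026. The cost is the loss of one supporting comparison.

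Running AVIRI offline on the stored control-arm photographs, taken with the same camera model, would let the descriptive estimates use all 500 randomised participants. It is optional, and the repair does not depend on it.
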